#### *Inclusion criteria*

• Eighteen years of age or older at the time of entry to the trial

• Able and willing to undertake all assessments required by the trial

• Good understanding of written and spoken English

• Poorer ear (ear to be implanted): 

– Acquired (post-lingual) severe-to-profound sensorineural hearing loss of <10 years duration

– Severe-to-profound deafness defined as having hearing threshold >90 dB HL at 1 & 4 kHz, and >65 dB at 0.5 kHz

– Minimal benefit from a hearing aid (see below)

• Better ear (contra-lateral ear): Normal or near-normal hearing. For the purposes of this trial this is defined as hearing thresholds with a pure-tone average (PTA) of ≤30 dB HL at 0.5, 1, & 2 kHz.

The process that will be used to determine minimal benefit from a hearing aid is illustrated in Figure 2. For those patients who use a hearing aid at the time of the screening interview, speech perception performance in the best-aided condition will be assessed using a method similar to that used for traditional cochlear implantation candidates [21]. Two lists of Bamford-Kowal-Bench (BKB) sentences will be presented at 70 dB Sound Pressure Level from a loudspeaker positioned in front of the patient while their normal hearing ear is occluded using a combination of an earplug and a circumaural muffler. Performance will be measured in terms of the proportion of keywords reported correctly. If less than 50% of keywords are reported correctly, the patient will be considered as receiving minimal benefit from their hearing aid. If the percentage of keywords reported correctly is 50% or greater, performance will be reassessed using two different BKB lists while the function of the normal hearing ear is further degraded using a combination of a masking noise presented at 50 dB(A) via an insert tube-phone and a circumaural muffler. If less than 50% of the keywords are reported correctly with masking, the patient will be considered as receiving minimal benefit from their hearing aid.

**Figure 2 F2:**
[figure not shown]
**Functional screening assessment.** A flow chart of the screening process concerned with assessing potential participants against the inclusion criterion governing the acceptable level of function in the impaired ear. If aidable, functional performance will be assessed while the NH ear is occluded using an earplug and circumaural mufflers. Should the level of function still fall outside criterion, performance will be assessed again but while a masking noise is also presented to the NH ear. Individuals who cannot be aided, either because it is deemed clinically inappropriate or because it is not possible fit an aid (e.g. few or no measurable audiometric thresholds), will be eligible for inclusion. NH: Normal Hearing.

For those patients who do not use a hearing aid at the time of the screening interview, an assessment will be made as to whether it would be clinically appropriate to provide amplification in the impaired ear. This assessment process will reflect current standard clinical practice. If the provision of a hearing aid would be clinically appropriate, the patient will be referred for hearing aid fitting to confirm whether the level of gain being called for can be obtained using any of the hearing aid models available on the NHS, and whether the prescription can be achieved. Verification of the prescription will be determined using real-ear measurements [25]. If the necessary gain can be provided and the prescription can be achieved, the patient will undergo a trial of a hearing aid at their local audiology centre before speech perception is assessed in their best-aided condition as described above. The duration of the trial will vary according to local practice but will last for a minimum of four weeks. If amplification is deemed inappropriate, or the necessary gain cannot be provided or achieved, the patient will be deemed to be unaidable and will be considered for inclusion in the trial.

Participants may have previous experience with using a CROS system. However, participants must have ceased use of any CROS system prior to entry into the study so that they may be evaluated in their unaided state during the baseline phase.

#### *Exclusion criteria*

• Evidence of middle-ear pathology based on otologic examination and tympanometry

• Medical or psychological conditions that contraindicate undergoing surgery

• Tinnitus as primary motivation for treatment

• Ossification or any other cochlear anomaly that might prevent complete insertion of the electrode array

• Hearing loss of neural or central origin, including auditory neuropathy and neurofibromatosis type II

• Additional handicaps that would prevent or restrict participation in the audiological evaluations

• Unrealistic expectations on the part of the participant regarding the possible benefits, risks, and limitations which are inherent to the surgical procedure and prosthetic device

• Unwillingness of the participant to comply with all of the trial requirements

• Any known factor which would limit the benefit obtainable from a cochlear implant

A participant will be withdrawn from the trial if there is a failure of the cochlear implant device or they experience a serious or intolerable device-related adverse event leading to the explant or discontinued use of the cochlear implant device. Participants may withdraw themselves from the trial at any time and without giving a reason. Participants who withdraw voluntarily during the CROS or cochlear implantation phases may continue to use their current device (CROS or cochlear implant) indefinitely.

### Interventions

#### *Contra-lateral routing of signals*

The CROS hearing aid comprises a conventional acoustic hearing aid and a remote microphone. The remote microphone is worn on the impaired ear and the hearing aid is worn on the non-impaired ear. Sounds arriving at the impaired ear are picked up by the remote microphone and sent via a wireless link to the hearing aid which delivers the sounds via air conduction to the non-impaired ear. The acoustic coupling for the hearing aid is selected to have the smallest possible impact on the sound arriving at the non-impaired ear.

The trial will use the Phonak CROS system (Phonak AG, Stäfa, Switzerland). The system will be fitted by an experienced audiologist using the standard fitting software provided by Phonak (Target™3.0). The fitting procedure ensures that the acoustic information at the non-impaired ear is similar regardless of whether a sound source is incident to the impaired or non-impaired ear [26,27]. The fit will be verified using real-ear measurements. At the time of fitting, participants will be encouraged to use the CROS system for as long as possible each day and to record the number of hours of use in their user diary each day. Participants will attend a follow-up appointment after one month of CROS use during which their initial usage will be assessed, additional encouragement will be given, and the fitting adjusted as required.

#### *Cochlear implant*

A cochlear implant comprises an externally-worn sound processor and a wholly-implantable receiver-stimulator. The receiver-stimulator is connected to a micro-electrode array that is surgically-inserted into the inner ear (cochlea). Sounds are picked up by one or more microphones in the sound processor and are separated into frequency bands containing both slow changes in amplitude over time (envelope) and rapid changes in frequency around the centre frequency of each band (fine structure). The sound processor extracts the envelope in each frequency band and uses the envelopes to define the pattern of pulses to be delivered by each electrode. The pulse patterns are delivered through the scalp to the implanted receiver-stimulator via a radio-frequency coil.

The trial will use the Cochlear^TM^ NucleusⓇ Cochlear Implant System (Cochlear Ltd, NSW, Australia). The NucleusⓇ CI442 implant will be implanted by experienced ENT surgeons. The implant system will be activated once the wound has healed, typically 3–6 weeks after surgery, and the sound processor will be fitted by an experienced cochlear implant audiologist. The programme of post-activation fitting and rehabilitation appointments will reflect the current standard care delivered to traditional cochlear implant candidates in the UK. Participants will be encouraged to use their cochlear implant for as long as possible each day and to record their actual usage in their user diary. Participants will also be encouraged to follow a rehabilitation programme which will include listening to speech materials fed directly into the sound processor of the implant via an accessory cable.

### Device fitting procedures

#### *CROS*

The CROS fitting procedure aims to preserve the resonance characteristics of the non-impaired ear and to overcome the head shadow which would otherwise attenuate sounds arriving at the impaired ear. The procedure requires the use of Real Ear Measurements (REMs). REMs will be carried out according to recommendations from the British Society of Audiology [25] and manufacturer-specific instructions based on the fitting hardware and software being used. This will include the choice of stimulus type, equipment setup, fitting environment, participant positioning, and probe calibration method.

The probe tube will be calibrated prior to commencing the fitting procedure. The procedure involves making three probe measurements [26]: 

1. A real-ear unaided response (REUR) while the loudspeaker is positioned 45 degrees towards the non-impaired ear. The probe tube and reference microphone are both situated at the non-impaired ear. The CROS system is not worn during this measurement.

2. A real-ear aided response (REAR 1) measured using the same setup as for the REUR. The CROS system is worn and turned on during this measurement.

3. A second real-ear aided response (REAR 2) measured while the loudspeaker is positioned 45 degrees towards the impaired ear. The probe tube is still situated at the non-impaired ear but the reference microphone is situated at the impaired ear.

The measurement REAR 1 will be compared to the REUR to confirm that the coupling of the hearing aid to the non-impaired ear is largely acoustically transparent. Any gross dissimilarity will be addressed by checking and reconsidering the method of acoustic coupling. The REAR 1 and REAR 2 measurements will be compared and checked to be within ±3 dB across the available frequency range. Any deviations between the two measurements will be addressed by adjusting the gain of the CROS system and repeating the measurement of REAR 2.

The available fitting hardware and software at each of the five trial sites may not permit the separation of probe tube and reference microphone on opposite sides of the head as required for the measurement of REAR 2. An alternative procedure has been described based on a stored equalisation method [27] and will be used where probe and reference cannot be separated.

#### *Cochlear implant*

The cochlear implant fitting procedure will follow the manufacturer-recommended procedure for fitting using the Custom SoundⓇ software. The default programming parameters specified by the manufacturer will be used unless the individual needs of a patient require a deviation from those parameters to maximise benefit. In general terms, the fitting procedure will involve checking electrode impedances, disabling electrodes based on impedance measurements and/or intra-operative findings, creating a mapping between input frequency bands and electrodes (MAP), and establishing the minimum detectable (threshold) stimulation level and the maximum comfortable stimulation level for each electrode.

Cochlear implant fitting is an iterative process to maximise hearing function, reflecting the emergence of hearing function over time due to a gradual acclimatisation and adaptation to electrically-delivered information. Participants will therefore attend several programming sessions in the initial months after activation of their implant through which their MAP, threshold levels, and comfort levels will be fine tuned to maximise speech understanding and acceptability to the patient.

### Primary outcome measures

Assessments of the ability to localise sounds and understand speech in noise will be administered using a purpose-built test setup [28-30] in an anechoic chamber at the MRC Institute of Hearing Research in Nottingham.

#### *Sound localisation*

Sound localisation will be measured in anechoic conditions and a range of reverberant conditions following established methods using a visual-pointing technique [31]. On each trial, a short pre-recorded speech segment will be presented from one of several loudspeakers positioned in the frontal plane and behind an acoustically-transparent curtain (Figure 3). Speech segments will be short isophonemic words [32] spoken by a male talker with a British accent. The task of participants will be to indicate the perceived location of the sound by moving a visual pointer projected onto the curtain. The position of the visual pointer will be adjusted using a computer-controlled trackball mouse and with a precision exceeding one degree of visual angle. Presentation levels will be roved from trial to trial to restrict the use of monaural loudness cues and limited so that stimuli do not engage the compression features of the cochlear implant sound processor which can degrade inter-aural level cues [33-35].

**Figure 3 F3:**
[figure not shown]
**Testing apparatus.** The apparatus that will be used to assess the sound localisation accuracy and speech understanding of patients in the trial. An array of loudspeakers and a visual projection system are positioned within an anechoic chamber. Thirty-six loudspeakers are distributed horizontally around the listening position with an additional 6 loudspeakers suspended above the listener and a further 6 loudspeakers positioned below the listener. The three visual projection screens are driven by three high-definition projectors. Responses are recorded using a trackball (localisation task) or through an intercom (speech understanding task).

The original speech waveforms will be presented after being convolved with the room impulse of a simulated room, the methods and parameters of which have been described previously [30]. The ratio between the direct and reverberant sound will be varied to simulate different room characteristics from anechoic (no reflections) to highly-reverberant. Localisation accuracy in anechoic conditions will reflect the ability of participants to access and use monaural spectral cues and inter-aural cues under ideal listening conditions. Comparison of localisation in anechoic conditions and in reverberant conditions will identify the level of reverberation that participants can tolerate while maintaining accuracy. Summary measures of localisation accuracy will be reported for each individual participant along with measures of bias and variance in their responses. The trial is powered using localisation data from a previous before-after study of cochlear implantation following CROS and simulated BAHD use [5].

#### *Speech understanding in noise*

Speech understanding in noise will be measured in terms of a speech-reception threshold (SRT) which represents the signal-to-noise ratio (SNR) at which 50% of sentences are reported correctly. Sentences will be drawn from a recording of the IEEE sentence corpus [36] spoken by a female talker with a British accent. The masking noise will be generated to match the long-term average spectrum of the sentences. SRTs will be measured using an adaptive procedure to avoid floor and ceiling effects by varying the level of the speech and noise from trial to trial based on the accuracy with which the participant recalls keywords in the sentences [37]. The spatial configuration of the speech and the noise will be varied across testing conditions to estimate the three main effects of two-eared listening to speech in noise [38]: i) the head-shadow effect estimated from the test conditions in which the speech is positioned on the side of the impaired ear and the noise is on the side of the non-impaired ear; ii) binaural squelch effect estimated from the test conditions in which the noise is positioned on the side of the impaired ear and the speech is on the side of the non-impaired ear; iii) binaural summation (redundancy) effect estimated from the test conditions in which the speech and noise are positioned equidistant from both ears; i.e. directly in front of the participant. SRTs will be reported for each individual participant along with a measure of the variance of the SNRs used to compute each SRT.

### Secondary outcome measures

#### *Hearing-specific quality of life questionnaires*

The Speech, Spatial and Qualities of Hearing Scale (SSQ) [39] contains 47 questions organised into three sections. The *Speech* section asks about difficulties with understanding speech in a range of everyday situations. The *Spatial* section asks about difficulties with localising sound sources and tracking moving sounds. The *Qualities* section asks about difficulties with the perceived naturalness of sounds, separating sounds, and the amount of effort required to listen. The SSQ has been found to be capable of distinguishing between groups of unilateral and bilateral hearing aid [40] and cochlear implant [41] users, confirming its sensitivity to spatial hearing abilities, and found to have a test-retest reliability of 0.83 [42].

Glasgow Hearing Aid Benefit Profile (GHABP) has been developed as a patient-centred outcome measure designed to measure the disability caused by a patient’s hearing loss before and after hearing aid fitting and the impact that the disability has on a patient’s everyday life [43,44]. The GHABP asks six questions about four specific listening situations and up to four listening situations nominated by the patient. Each question is a five-point Likert scale. The six questions correspond to the six domains of initial disability, impact on life (handicap), device use, device benefit, residual disability, and device satisfaction.

The Glasgow Benefit Inventory (GBI) is an instrument for measuring changes in quality of life as a result of otorhinolaryngological interventions [45]. The GBI is designed to be administered after the intervention has been received and provides a direct measure of its effect on the health state of the patient. The 18 questions are grouped to form three sub-scales: general, social support, and physical health. The GBI has been found to be responsive to unilateral cochlear implantation [46].

Tinnitus Functional Index (TFI) has been designed to measure treatment-related changes in tinnitus intrusiveness and severity. The development of the TFI has included the definition of the minimum clinically-important change in TFI score (13 points) and identified a test-retest reliability of 0.78 [47].

A user diary will also be provided in booklet form for the 3-month trial of the CROS system and for the 9-month follow-up period after cochlear implantation. Participants will be instructed to record the duration of their device use on a daily basis and will also be encouraged to record any comments about situations in which either intervention was particularly helpful or unhelpful.

#### *Generic quality of life questionnaires*

The Health Utilities Index Mark 3 (HUI3) is a generic preference-based method for describing health status and measuring health-related quality of life [48]. The HUI3 health status classification system describes an individual’s health state on eight dimensions of health: vision, hearing, speech, ambulation, dexterity, emotion, cognition, and pain. The utility value for a chronic health state described using the classification system can be calculated using the HUI3 multi-attribute utility function. The multi-attribute function has been derived based on the preferences of a sample of the Canadian general public [49,50]. Utility values are defined by a scale on which death has a value of 0 and perfect or optimal health has a value of 1. Utility values derived using the HUI3 are suitable for use as part of a health-economic analysis. The HUI3 has been found to be responsive to interventions for hearing loss including acoustic hearing aids [51,52] and cochlear implants [53].

The EQ-5D is a generic method for describing and valuing health states [54,55]. The EQ-5D has two components. The first component is a system for describing a health state on five dimensions of health: mobility, self-care, usual activities, pain/discomfort, and anxiety/depression. A single utility value or ‘tariff’ for a health state can be calculated using a model which describes the preferences of a sample from the UK population [56]. The second component is a visual-analogue scale (VAS) used to obtain the patient’s own opinion of their current health state. The EQ-5D has been found to be unresponsive to changes in health-related quality of life arising from severe-to-profound deafness [57] and provides smaller estimates for the change in utility after cochlear implantation compared to the HUI3 [46]. However, the EQ-5D is the preferred instrument of the UK National Institute for Health and Care Excellence (NICE) for measuring health-related quality of life [58].

### Statistical methods, data analysis and reporting

Analysis of the trial data will include all patients who pass the inclusion and exclusion criteria and will be conducted on an intention-to-treat basis. Participants who are withdrawn at any stage will be replaced. Participants who choose to leave during the baseline or CROS phases of the trial will be replaced. Participants who choose to leave after receiving a cochlear implant will not be replaced. Data from participants who choose to leave will be retained and included in the analyses of individual trial phases; i.e. baseline, CROS, and cochlear implantation. Due to the small sample size, missing data will not be imputed when conducting within-subject comparisons of the incremental change from baseline to CROS and from CROS to cochlear implantation. Drop-out rates at each phase of the trial will be reported as a marker of potential bias in the between-phase comparisons.

Baseline characteristics of the participants will be reported including (but not limited to) age, gender, audiometric thresholds, aetiology and history of hearing loss, duration of severe-to-profound deafness, and history of hearing aid use.

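### Participants withdrawn for implant failure or device-related explant are replaced, so the implant-versus-CROS estimate is not intention-to-treat and leans towards benefit

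*Protocol article*

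**What the plan says.** Two parts of the protocol article bear on this.

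The paragraph closing the *Exclusion criteria* section sets the rule for enforced withdrawal: "A participant will be withdrawn from the trial if there is a failure of the cochlear implant device". The same sentence adds a second trigger, a "serious or intolerable device-related adverse event leading to the explant or discontinued use of the cochlear implant device". Both can arise only after implantation.

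The section *Statistical methods, data analysis and reporting* says that the analysis covers all patients who meet the entry criteria and "will be conducted on an intention-to-treat basis". It then sets these rules:

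- Enforced withdrawals: "Participants who are withdrawn at any stage will be replaced".
- Voluntary leavers after implantation: "Participants who choose to leave after receiving a cochlear implant will not be replaced".
- Data retention: "Data from participants who choose to leave will be retained and included in the analyses of individual trial phases". Nothing is said about data from participants who are withdrawn.
- Missing values: "missing data will not be imputed when conducting within-subject comparisons of the incremental change from baseline to CROS and from CROS to cochlear implantation".
- The rate of loss in each phase is to be reported as a sign of possible bias.

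The *Efficacy analysis* section places the primary analysis at the end of the 9 months after implantation and compares the implant phase with the CROS phase within subject.

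**The concern.** An intention-to-treat estimate keeps people in the analysis whatever becomes of their treatment. Here the only stated triggers for enforced withdrawal are bad results of the implant itself, and people withdrawn for them are refilled even after implantation. People who leave after implantation by choice are not refilled. The losses that say most about the implant are thus the ones that vanish from the cohort.

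The primary contrast would then estimate the gain in people without device failure or device-related explant, under a label that promises the gain in everyone treated. The article says that the trial reflects an expected NHS care pathway, is unlikely to be repeated, and should inform later cost-effectiveness work. Readers with those purposes need the average over everyone implanted.

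**Working it through.** **1. The plan's own sample size.** Inputs from *Population and sample size*: effect size 1.63 SD, one-tailed Wilcoxon signed-rank test, α = 0.05, power 95%, stated n = 7, raised to 10 to allow for attrition after implantation. Simulating the exact one-sided test (200,000 runs, differences normal with mean 1.63 and SD 1) gives power of 94.5% at n = 6, 96.8% at n = 7 and 99.8% at n = 10. The stated 7 is reproduced. The plan can lose 10 − 7 = 3 pairs and still meet its target.

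**2. Following one participant through the rules.** Suppose the implant fails between activation and the 9-month test.

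- *Exclusion criteria*: the participant is withdrawn.
- *Efficacy analysis*: the primary value is the 9-month one, which no longer arises.
- *Statistical methods*: no value is imputed, so there is no implant-minus-CROS pair. The retention sentence does not reach this person. A replacement is recruited and, if implanted, supplies a pair.

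The opening sentence of *Statistical methods* nevertheless counts this participant in the analysis. The statements cannot all hold for the primary comparison. A failure after the 9-month test does no harm, because the pair is already complete.

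**3. Size of the bias.** The documents give neither a failure rate nor the outcome after failure, so both are assumed. Let *g* be the mean gain with a working implant, and let a failed implant give zero gain over CROS. With *k* failures among the first 10 implanted:

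- mean over all ten = *g* × (10 − *k*)/10
- mean over working implants only = *g*
- overstatement = 10/(10 − *k*) − 1

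| *k* | All ten, with *g* = 1.63 SD | Working only | Overstatement |
|---|---|---|---|
| 1 | 1.63 × 0.9 = 1.47 SD | 1.63 SD | 11% |
| 2 | 1.63 × 0.8 = 1.30 SD | 1.63 SD | 25% |

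If the per-patient risk before 9 months is *p*, the expected gain over everyone implanted is (1 − *p*)*g*, and the overstatement is 1/(1 − *p*) − 1:

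| Assumed *p* | Overstatement of expected gain | Chance of ≥1 failure in 10, 1 − (1 − *p*)^10 | Chance of ≥2 in 10 |
|---|---|---|---|
| 2% | 2.0% | 18% | 1.6% |
| 5% | 5.3% | 40% | 8.6% |
| 10% | 11.1% | 65% | 26% |

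The result depends on the zero-gain assumption. If a failed implant left people 1 SD worse than with CROS, one failure would give (9 × 1.63 − 1)/10 = 1.367 SD, an overstatement of 1.63/1.367 − 1 = 19%.

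**4. What replacement adds.** Without replacement, the complete pairs would still average *g*, because the failures would still be missing. Replacement restores the headcount and so hides the loss. Ending it is therefore not enough on its own; the analysis set has to be defined as well.

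**5. Is replacement needed for power?** With all 10 analysed and failures drawn from a normal distribution with mean 0 and SD 1, simulated power is 98.5% with one failure and 93.6% with two. These figures are only a guide to the fix below, which scores exact zeros.

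**The case against.** The strongest reply has four parts.

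*The bias is disclosed.* Drop-out rates will be reported by phase, and adverse events are reported separately. This is a real safeguard and should be credited. It tells readers that people are missing, but it does not put them back into the estimate.

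*Nothing says that withdrawn participants' data are thrown away.* That is correct. A reader might infer a rule to discard them, and the text contains none. They drop out of the primary pair because the 9-month value is absent, nothing is imputed, and retention is promised only to voluntary leavers.

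*The rule is narrower than it first looks.* A reader might infer that anyone who stops using the implant is withdrawn and replaced. The text does not support this: discontinued use counts only when a serious or intolerable device-related adverse event leads to it. A reader might also infer that voluntary leavers are removed because of their outcome. The documents do not support that either. Such people may go without giving a reason, are not replaced after implantation, and keep their data in the single-phase analyses. Declining to impute for them in a paired comparison of about ten people is a stated choice, not an error.

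*The effect may be nil.* With no device failure, no one is affected. At the assumed risks, the overstatement of the expected gain is modest, and the significance test would seldom change. This stands, and it limits the severity. It does not remove the contradiction.

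**Conclusion.** The point holds in a limited form. Replacing participants withdrawn for device failure or device-related explant or discontinuation, with no imputation, is inconsistent with the declared intention-to-treat basis and tilts the implant-minus-CROS estimate towards benefit. It applies only to events before the 9-month test.

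Under the zero-gain assumption, the expected overstatement is about 2%, 5% or 11% at assumed risks of 2%, 5% or 10%. It is about 11% if exactly one of ten fails and 25% if two do. The documents supply neither the risk nor the outcome after failure, so these are illustrations and not predictions.

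A reader might go further and conclude that the trial's positive test could be an artefact of replacement. Nothing in the documents supports that. The main damage is to the size and meaning of the estimate. This should be fixed, but it does not by itself invalidate the trial.

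**What to change.** Reconcile the withdrawal paragraph under *Exclusion criteria* with *Statistical methods, data analysis and reporting*. The change concerns analysis and recruitment only; the clinical reasons for withdrawal need not be altered.

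- Remove replacement after implantation. Replacement during the baseline and CROS phases can stay.
- Define the implant-versus-CROS analysis set as every implanted participant.
- Use the 9-month result wherever it exists. Where device failure or device-related explant prevents it, score no gain over CROS and keep that score in the mean gain.
- Use a signed-rank method that retains zeros, such as Pratt's. Standard Wilcoxon handling deletes exact zeros and would drop these participants from the test again.
- Do not carry forward a 3-month value from a device that later failed, because that credits a gain since lost.
- Report the complete-pair, working-device result as a sensitivity analysis.

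If replacement after implantation is kept, drop the intention-to-treat label and state that the estimate applies to participants without device failure or device-related explant.

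The cost is a change of wording and a slightly less favourable estimate if failures occur. No extra implants are needed, and the margin of 10 over the required 7 was set aside for attrition in this period.
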